Cumulative live-birth rate within three years from first treatment (surgery or ART treatment).

Definition of primary outcome measure

CLBR is defined as any live births from first treatment until end of follow up (three years from first ART treatment or surgery or drop out from the study, whichever comes first).

Primary outcome will be calculated considering also the following pre-specified subgroups: study center,  type of ART-treatment (IVF or ICSI), age (< and > 35 years), ovarian reserve ( anti-mullerian hormone (AMH) <0.5ng/L, 0.5-3.5 ng/L and AMH >3.5ng/L ) (35) adnexal surgery (yes/no), surgery on deep endometriosis anterior compartment (yes/no) or deep endometriosis posterior compartment (yes/no) (defined by Classification of surgery, “Klassifikation av vårdåtgärder” (KVÅ codes), see appendix).

SECONDARY OUTCOME MEASURE

- Cumulative Pregnancy Rate (CPR)
- Time to pregnancy and live birth
- Spontaneous Pregnancy Rate
- Miscarriage rate and/or extrauterine pregnancies
- Reproductive outcomes per IVF cycle
- Rate of recurrent implantation failure (RIF), (20) evaluated at the end of the study period
- Infections after oocyte pick-up
- Quality of life and pain
- Peri- and two months postoperative complications classified by Clavien-Dindo and Classic systems
- Health care costs
- Obstetrical outcomes and complications
- P-progesterone levels on day of embryo transfer at first HRT frozen-thawed artificial embryo transfer cycle

Definition of secondary outcome measures

Cumulative Pregnancy Rate (CPR) is defined as all pregnancies confirmed with ultrasound, from first treatment (surgery or ART) until three years of follow up.

Time to pregnancy is defined as time from first treatment (surgery or ART) to first pregnancy confirmed with ultrasound. Time to live birth defined as time from first treatment (surgery or ART) to first livebirth.

Spontaneous pregnancy rate is defined as any spontaneous pregnancy occurring between first treatment and end of follow-up.

Miscarriage rate defined as frequency and proportion of spontaneous loss of any clinical and biochemical pregnancy before week 22 and/or extrauterine pregnancy defined as a pregnancy not located in the uterine cavity, occurring between first treatment and end of follow-up.

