Reproductive outcome per IVF/ICSI-cycle: number of oocytes retrieved (mature and/or total), fertilization rate, Fresh embryo transfer (ET) (day 2, day 3, day 5), number of blastocysts cryopreserved, pregnancy rate per ET, live birth rate per ET, miscarriage rate per ET, cumulative pregnancy rate per cycle, cumulative miscarriage rate per cycle, cumulative live birth rate per cycle.

RIF (recurrent implantation failure) evaluated at the end of the study period. RIF is defined here as no pregnancy after three ETs in women <35 years and four ETs in women 35-39 years old (20).

Infections after oocyte pick-up will be registered yes/no and further classified as requiring i) treatment with antibiotics, ii) readmission or iii) surgical intervention.

Health related quality of life (HRQoL) and pain will be assessed by questionnaires, Endometriosis Health Profile (EHP-30), EQ5D and Numeric Rating Scale (NRS), completed by study participants preferably as electronical patient reported outcome measures or during the clinic visit (by manually filling in forms, by accessible computer or by mail). The assessments are performed maximum one month before the first intervention, at the time of oocyte retrieval, two months after ART or surgery and at three-year follow-up.

Intraoperative complications will be classified by Classic systems (21).

Two months postoperative complications will be defined according to the Clavien-Dindo (22) system.

Health care costs from randomization to end of trial: Direct costs will be used by assessing internal accounting and billing systems within the hospitals, cost per patient (CPP). We will also measure the quality-adjusted life years (QALYs) gained with the intervention and use this to undertake a cost-utility analysis. The QALY calculations will be based on fertility status measures for trial participants, with valuations of changes in fertility status and quality of life based on the EQ-5D.

Obstetrical outcomes and complications defined as:

- pregnancy- related complications: premature delivery, preeclampsia, gestational diabetes, placenta previa, placenta ablation, placenta spectrum disorders
- delivery-related complications: emergency caesarean section, pelvic floor trauma, delivery related bleeding, manual placenta removal

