*Assisted reproductive technologies data (for each IVF/ICSI-cycle, max 3):*

- Complication – yes/no
- Type of complication (infection, ovarian hyperstimulation syndrome (OHSS), bleeding)
- Time from surgery to first oocyte pick-up
- Type of IVF protocols (GnRH agonist protocol/GnRH antagonist protocol)
- Total dose/mean daily dose of follicle stimulating hormone (rFSH) /human menopausal gonadotropin (hMG)
- Duration of IVF stimulation (days)
- Cancelled cycle (before or after oocyte pick up (OPU)) (excluding freeze all cycles)
- Reason of cancelled cycle
- Type of ovulation triggering [GnRH agonist (Gonapeptyl/Suprecur/Suprefact/Synarela) / Ovitrelle]
- Date of OPU
- Freeze all cycle (yes/no) and reason of that
- Number of retrieved oocytes (GV/MI/MII)
- Performed fertilisation method (ICSI/IVF)
- Sperm – fresh vs frozen
- Donor sperm – yes/no
- Origin of sperm – ejaculated/ epidydimal / testicular
- Oocytes – fresh vs frozen
- Number of inseminated oocytes
- Number of fertilised oocytes
- Number of good quality embryos defined according to Gardner criteria as AA, AB and BB for blastocysts (23) or top and good quality based on the number of blastomeres, the fragmentation rate and the multinucleation of blastomeres for cleavage stage embryos (24).
- Number of frozen blastocysts (D5 or D6)
- Date for fresh embryo transfer
- Embryo age at fresh embryo transfer (D2, D3, D4, D5 or D6)
- Number of embryos transferred (SET/DET)
- Type of embryo transfer (Fresh/Frozen)
- Type of protocols for Frozen-thawed ET (Natural Cycle (NC), HRT, Letrozol-stimulated, gonadotropinstimulated)
- Use of GnRH downregulation in Frozen-thawed HRT cycle (yes/no, number of days)
- Total estrogen dose and type of estrogen preparations in HRT FET-cycle
- Endometrial thickness prior to embryo transfer in HRT-FET
- Cycle day of endometrial thickness measurement in HRT-FET
- P progesterone level on the day of ET in HRT-FET
- Date of frozen ET
- Urinary pregnancy test (positive/negative)
- Gestational age at pregnancy ultrasound
- Fetal heartbeat at ultrasound (present/absent)
- Number of foetuses
- Number of gestational sacs
- Result foetus 1 (miscarriage, abortion, ectopic pregnancy, delivery)
- Date for delivery / end of pregnancy foetus 1
- Result foetus 2 (miscarriage, abortion, ectopic pregnancy, delivery)
- Date for delivery / end of pregnancy foetus 2
- Result foetus 3 (miscarriage, abortion, ectopic pregnancy, delivery)
- Date for delivery / end of pregnancy foetus 3

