In Sweden in 2023, 9.9% of patients undergoing surgery for endometriosis within the framework of national highly specialized care experienced mild complications Clavien Dindo 1-2 (e.g. infection and hematoma at the surgical site), and 3.3% experienced serious complications Clavien Dindo 3 (e.g. bowel leakage, unexpected bladder injury, ureteral injury, or intra-abdominal bleeding requiring reoperation) (38). Serious complications may, in rare cases, necessitate further surgical interventions. The risk of complications varies slightly depending on the location of the endometriosis (38).

Patients undergoing surgery will need to delay ART treatment by two to three months in order to fully recover.

FERTILITY TREATMENT WITH ART

ART treatments will be carried out at Swedish reproductive units authorized to provide publicly funded fertility care. The majority of treatments are expected to take place at the university-affiliated reproductive clinics in Stockholm, Gothenburg, Skåne, and Uppsala. However, for participants residing in other regions of Sweden, undergoing treatment locally offers a significant advantage by reducing the logistical and emotional burden of long-distance travel to these central clinics. To ensure equitable access and minimize patient stress, regional ART centers will be considered when appropriate.

One IVF/ICSI-cycle is defined as the transfer of all the embryos created via that particular oocyte pick-up until pregnancy confirmation or until the failure of the last embryo transfer. In case of a cancelled cycle prior to oocyte pick-up it will not be counted. The duration of one IVF-cycle depends on the number of embryo transfers and typically ranges between two and nine months.

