ART treatment: Women allocated in the ART arm will undergo up to three cycles of controlled ovarian stimulation (COS) followed by oocyte retrievals and embryo transfers. In Sweden, ART-treatment costs for women under the age of forty and without having children in current relationship are covered by the tax-funded healthcare system, with up to 3 IVF/ICSI treatments, given that they are considered medically meaningful, and that each stimulation is started before the woman turns 40 years of age (39). In case the treatment results in cryopreserved embryos, it is planned that they should be transferred prior to the start of any new COS. Women will be managed according to a routine clinical protocol at each reproductive unit. Stimulation protocols will be chosen individually by clinicians, taking into consideration age and ovarian reserve of each woman, as it is a standard routine in the collaborating Reproductive Units. No aspiration of endometrioma prior to oocyte pick-up will be performed. Antibiotic prophylaxis at the day of oocyte pick-up will be given according to local guidelines.

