# STATISTICAL CONSIDERATIONS

The primary exposure is the randomized allocation (surgery prior to ART vs ART alone). All analyses will follow the intention-to-treat (ITT) principle, meaning participants are analyzed according to their randomized group regardless of adherence. Per-protocol and as-treated analyses will be conducted as sensitivity analyses to assess robustness. An interim analysis at the halfway point is planned to monitor potential adverse effects and ensure the safety of the interventions.

No formal adjustment for multiplicity will be made; the primary endpoint will be tested at a two-sided α=0.05, while secondary endpoints are considered supportive and exploratory. Sensitivity analyses will address protocol deviations, handling of missing data, and robustness to alternative modelling approaches.

DATA ANALYSES

Baseline demographic and patient’s characteristics will be summarized by treatment group. Continuous variables will be described with mean, standard deviation, median, interquartile range, minimum and maximum, and categorical variables with counts and percentages.

Primary endpoint

The primary endpoint of the study is the Cumulative Live Birth Rate (CLBR), defined as the proportion of participants achieving at least one live birth within three years following the initiation of treatment.

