**Cycle-Specific Outcomes**

Live birth and pregnancy rates per IVF/ICSI cycle will be analyzed using log-binomial regression or modified Poisson regression with robust variance to account for within-patient correlation. Other cycle-specific outcomes (e.g. number of oocytes retrieved, fertilization rate, embryo transfer characteristics, miscarriage rates) will be summarized descriptively and compared between groups using appropriate regression models.

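### The definition of an IVF/ICSI cycle stops at pregnancy confirmation, so a birth from the same pick-up's remaining embryos after a pregnancy loss is credited to no cycle, and the cumulative live birth rate per cycle can only be understated

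*Protocol*

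**What the plan says.** Protocol, Study Treatment, Fertility treatment with ART, defines a cycle as "the transfer of all the embryos created via that particular oocyte pick-up until pregnancy confirmation or until the failure of the last embryo transfer". A cycle cancelled before pick-up is not counted. On frozen embryos the same section says: "In case the treatment results in cryopreserved embryos, it is planned that they should be transferred prior to the start of any new COS".

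Study Objectives, Definition of secondary outcome measures, lists among the per-cycle reproductive outcomes "cumulative pregnancy rate per cycle, cumulative miscarriage rate per cycle, cumulative live birth rate per cycle". It gives no separate rule for assigning a transfer or a birth to a cycle. The miscarriage definition in the same part covers "spontaneous loss of any clinical and biochemical pregnancy before week 22", so losses after a pregnancy has been established are expected.

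Statistical Considerations, Cycle-Specific Outcomes, states: "Live birth and pregnancy rates per IVF/ICSI cycle will be analyzed using log-binomial regression", with modified Poisson regression as the alternative and robust variance for repeated cycles in one woman.

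The primary endpoint is per woman: "the proportion of participants achieving at least one live birth within three years following the initiation of treatment".

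**The concern.** A cumulative live birth rate per cycle is meant to show what one pick-up yields once its fresh and frozen embryos have been used. The stated cycle ends earlier, at confirmation of a pregnancy, and live birth is not one of its end points.

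Take a woman whose first transfer gives a confirmed pregnancy that is then lost, and who has blastocysts frozen from the same pick-up. Her next transfers come after that cycle's stated end. They cannot open a new cycle, because there has been no new pick-up. If one of them leads to a child, the cycle is still scored as having no live birth.

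The omission follows only from pregnancy loss, so it need not be equal between arms. The protocol hypothesises fewer miscarriages when surgery comes first. If that is true and the other rates are similar, more births would be left out of the first-line ART arm, and the per-cycle comparison would tilt towards surgery.

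**Working it through.** **Tracing the rule.** The documents state no per-cycle rate, so there is no figure to reproduce.

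1. The cycle is a set of transfers from one pick-up, closed by pregnancy confirmation or by failure of the last transfer.
2. A confirmed pregnancy closes it. No text reopens it after a loss.
3. Remaining frozen embryos are used before new stimulation, so these transfers precede the next pick-up.
4. They therefore lie between two cycles and belong to neither.

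**Size.** All four inputs are assumptions:

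- p: confirmed pregnancy per cycle
- m: share of those pregnancies lost after confirmation
- f: share of the women with a loss who have embryos left from that pick-up
- l: later live birth from those embryos

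Rate under the rule as written = p(1 − m). Births left out = p × m × f × l. Rate counting all embryos of the pick-up = the sum of the two.

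| Case | p, m, f, l | As written | Left out | All embryos counted |
|---|---|---|---|---|
| Low | 0.30, 0.10, 0.30, 0.20 | 0.30 × 0.90 = 27.0% | 0.18 points | 27.2% |
| Middle | 0.40, 0.20, 0.45, 0.30 | 0.40 × 0.80 = 32.0% | 1.08 points | 33.1% |
| High | 0.50, 0.30, 0.60, 0.40 | 0.50 × 0.70 = 35.0% | 3.6 points | 38.6% |

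The left-out term is a product of proportions and cannot be negative, so the error has one direction.

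**Effect on the comparison.** Hold p = 0.40, f = 0.45 and l = 0.30 in both arms, with loss of 20% in one arm and 10% in the other.

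- As written: 0.40 × 0.80 = 32.0% and 0.40 × 0.90 = 36.0%. Ratio 36.0/32.0 = 1.13, difference 4.0 points.
- All embryos counted: 32.0 + 1.08 = 33.08% and 36.0 + 0.54 = 36.54%. Ratio 36.54/33.08 = 1.10, difference 3.46 points.

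The rule adds 4.0 − 3.46 = 0.54 points to the difference in this example.

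**Other per-cycle outcomes.** If each outcome is scored as at least one event per cycle, a cycle with a confirmed pregnancy that miscarried already counts for both cumulative pregnancy and cumulative miscarriage. Later transfers cannot change either. Only live birth changes.

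**The case against.** The strongest reply is that the rule was never meant to cut off outcomes. Every live birth comes after confirmation, so a cumulative live birth rate per cycle already requires later events to be credited back to the pick-up. The definition speaks of all embryos from the pick-up and joins its two end points by a plain *or*. The primary outcome definition, by contrast, says which of its end points governs. On that view the cycle simply continues after a loss.

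That reading is possible, but the protocol nowhere states it. What the definition delimits is the set of transfers. The outcome of a transfer inside the set follows naturally, but a transfer made after the set has closed is not in it. The typical length given for a cycle, two to nine months, shows no sign of allowing for a pregnancy, a loss and further transfers. If both readings are open, two analysts could report different rates from the same data.

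A second reply is that such detail belongs in the SAP, which is not at hand. The SAP may well settle it. But the protocol has not left the unit open: it states one, and that unit does not fit its own cumulative outcome.

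A third reply stands in large part: the consequence is limited. Secondary endpoints are declared supportive and exploratory, the per-transfer rates still capture these transfers, and the planned ART data include pick-up, transfer and delivery dates. The births could be reassigned later. Against this, the data are to be recorded per cycle with a maximum of three, so a transfer that belongs to no defined cycle has no clear place, and sites may enter it differently.

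Four stronger inferences are not supported:

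- **That the primary result is biased.** It is per woman over three years and does not use the cycle definition.
- **That all three cumulative per-cycle outcomes are distorted.** With at-least-one-event scoring only live birth is.
- **That per-cycle births ought to add up to the per-woman rate.** The latter counts women, and its births are not restricted to those from ART, so the two would not reconcile under any cycle definition.
- **That the loss is as large as a count per confirmed pregnancy suggests.** In the middle case that count is 0.20 × 0.45 × 0.30 = 2.7%, but the outcome is per cycle, where it is 0.40 × 2.7% = 1.08 points.

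**Conclusion.** The point holds for one secondary outcome. Read as written, the cycle definition leaves out live births from a pick-up's remaining embryos after a pregnancy loss, so cumulative live birth rate per cycle can only be understated. The understatement is greater in the arm with more losses, provided the pregnancy rate, surplus-embryo share and later birth rate are similar between arms.

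The documents supply none of these rates. Under the assumed ranges the understatement is about 0.2 to 3.6 percentage points per cycle. With losses of 20% versus 10%, the ratio between arms is 1.13 instead of 1.10. This is probably modest, and it is not evidence of any actual difference between the arms.

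The primary cumulative live birth rate and the sample size do not depend on the cycle definition. A related gap is that the definition does not say whether confirmation means the urine test or ultrasound. If it means ultrasound, a biochemical loss does not close the cycle and fewer transfers are affected. If it means the urine test, more are.

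**What to change.** For the cumulative per-cycle outcomes, define a cycle as one oocyte pick-up plus all fresh and frozen transfers of its embryos, until the first live birth, until no embryos remain, or until end of follow-up. State that a pregnancy loss does not close the cycle, and attribute each transfer to its pick-up of origin in the eCRF. Use the same sentence in the SAP, and say there that each outcome is scored as at least one event per cycle, if that is the intention.

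This changes an analysis definition only. Care, the number of treatments offered and the order in which embryos are used stay as they are. The cost is one sentence and one linking field in the eCRF, with no extra visits or clinical data. It is best settled before much data entry, so that sites record transfers after a loss in the same way.

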# STUDY OBJECTIVES

HYPOTHESIS

First line surgery (prior to ART treatment) in women with endometriosis AAGL stage III-IV will result in improved cumulative live birth rate (CLBR) as compared to first line ART.

PRIMARY OBJECTIVE

To assess whether surgery conducted prior to ART in women with endometriosis AAGL stage III-IV increases chances of CLBR as compared to first line ART.

.

SECONDARY OBJECTIVES

To evaluate whether surgery prior to ART treatments in women with endometriosis AAGL stage III-IV will result in improved cumulative pregnancy rate (CPR) and lower miscarriage rate as compared to first line ART.

To compare whether surgery prior to ART treatments in women with endometriosis AAGL stage III-IV will result in shorter time to live birth or pregnancy as compared to first line ART.

To investigate if surgery prior to ART treatments in women with endometriosis AAGL stage III-IV will result in better reproductive outcomes per IVF cycle and a lower rate of recurrent implantation failure (RIF).

To assess if surgery prior to ART treatments in women with endometriosis AAGL stage III-IV will result in lower rate of infections after oocyte pick-up requiring treatment with antibiotics as compared to first line ART?

To evaluate if surgery prior to ART treatments in women with endometriosis AAGL stage III-IV result in higher Quality of life and less pain measured with Endometriosis Health Profile (EHP-30) and Numeric Rating Scale (NRS) before ART, i) at the time of oocyte retrieval, ii) two months after ART and iii) at the three-year follow-up visit as compared to first line ART.

To explore whether surgery prior to ART treatments in women with endometriosis AAGL stage III-IV will be cost effective compared with first line ART?

To examine if surgery prior to ART treatments in women with endometriosis AAGL stage III-IV will result in reduced pregnancy and delivery complications, as well as fewer complications within 8 weeks postpartum, compared to first line ART.

To investigate whether serum progesterone level on the day of frozen embryotransfer in hormone replacement cycles in patients with severe endometriosis is associated with reproductive outcomes (LBR, pregnancy rate, miscarriage rate) and to determine if there is any difference in p-progesterone level between the two different study groups first line ART vs first line surgery in women with endometriosis AAGL stage III-IV?

PRIMARY OUTCOME MEASURE

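### The per-cycle secondary outcomes are compared only among cycles that reach oocyte pick-up, a post-randomisation event that surgery may alter

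*Protocol*

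**What the plan says.** In the protocol, Study Treatment (Fertility treatment with ART) fixes the unit: "One IVF/ICSI-cycle is defined as the transfer of all the embryos created via that particular oocyte pick-up". Shortly afterwards it adds: "In case of a cancelled cycle prior to oocyte pick-up it will not be counted".

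The secondary objectives use that unit for a comparative question, asking whether surgery before ART "will result in better reproductive outcomes per IVF cycle and a lower rate of recurrent implantation failure (RIF". The definitions of the secondary outcomes list oocytes retrieved, fertilisation and "cumulative pregnancy rate per cycle, cumulative miscarriage rate per cycle, cumulative live birth rate per cycle". Under Cycle-Specific Outcomes the comparison is specified: "Live birth and pregnancy rates per IVF/ICSI cycle will be analyzed using log-binomial regression or modified Poisson regression with robust variance", the robust variance being there for within-patient correlation. Statistical Considerations opens its analysis policy with "All analyses will follow the intention-to-treat (ITT) principle".

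Two other places treat a cycle differently. The definition of the start of trial and the first footnote to the schedule of events both place the start of the first ART cycle at the first FSH injections. The list of ART data, to be recorded for each cycle up to three, includes "Cancelled cycle (before or after oocyte pick up (OPU)) (excluding freeze all cycles" and the reason for cancellation.

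**The concern.** A woman reaches pick-up only if she starts ART and her stimulation is not cancelled. Both steps come after randomisation, and the protocol gives grounds for thinking that either could differ by arm.

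- **Cancellation.** The surgical section aims to limit harm to organ function and mentions gentler techniques where ovarian reserve is already reduced. It does not discuss cancellation. An effect of ovarian surgery on response, and through response on cancellation, is a plausible inference, but the protocol does not state one.
- **Conception before ART.** The background calls spontaneous pregnancies after surgery for deep endometriosis frequent, and the surgical section links cyst enucleation to better chances of spontaneous conception. Only the surgery arm has a planned interval, of two to three months, between its first treatment and ART. A woman who conceives then and never has a pick-up supplies no cycle.

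Randomisation does not protect a comparison of the cycles that remain. Second and third cycles come mainly from women whose earlier cycles failed, which adds a further layer of selection. Robust variance deals with correlation between cycles of the same woman, not with selection into the set of cycles. At stake is the answer to a stated secondary objective, which could be biased for or against surgery.

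**Working it through.** **The plan's own figures.** The protocol gives no rate for cancellation, for conception before ART or for live birth per cycle, so there is no figure on this point to reproduce. Its one related calculation is the sample size for the per-woman primary endpoint (55% v 71%, two-sided 5%, 80% power). With pooled variance, n per arm = [1.96·√(2·0.63·0.37) + 0.842·√(0.55·0.45 + 0.71·0.29)]² / 0.16² ≈ 141.8, so 142 as stated. The point here does not depend on it. All rates below are assumptions.

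**Check 1: cancellation before pick-up.** Let p be live birth per pick-up and c the share of started stimulations cancelled before pick-up. Then:

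- rate per start = p × (1 − c)
- RR per start = RR per pick-up × (1 − c_surgery) / (1 − c_ART)

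With p = 0.30 in both arms, the per-pick-up RR is 1.00. Per start:

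- 5% v 10% cancelled: 0.30 × 0.95 = 0.285 and 0.30 × 0.90 = 0.270; RR = 0.270/0.285 = 0.95
- 5% v 15%: 0.285 and 0.30 × 0.85 = 0.255; RR = 0.255/0.285 = 0.89
- 10% v 20%: 0.270 and 0.240; RR = 0.240/0.270 = 0.89
- equal cancellation in both arms: RR = 1.00, no distortion

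The value of p cancels out of the ratio; only the two cancellation rates matter. If instead live birth per start is equal, the per-pick-up RR is 0.95/0.90 = 1.06 at 5% v 10% and 0.95/0.85 = 1.12 at 5% v 15%, apparently favouring surgery. Lower cancellation after surgery would reverse both patterns.

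**Check 2: conception before ART.** Assume that half the women have a 40% and half a 20% chance of live birth in a first cycle, and that surgery leaves these chances unchanged. The ART arm then has 0.5 × 0.40 + 0.5 × 0.20 = 0.30. Let a fraction f of the surgery arm, all from the better half, have a live birth from conception before ART.

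- f = 0.05: entrants (0.45 × 0.40 + 0.50 × 0.20)/0.95 = 0.28/0.95 = 0.295; RR per first cycle 0.98. Per randomised woman 0.05 + 0.28 = 0.33; RR 1.10.
- f = 0.20: entrants (0.30 × 0.40 + 0.50 × 0.20)/0.80 = 0.22/0.80 = 0.275; RR per first cycle 0.92. Per randomised woman 0.20 + 0.22 = 0.42; RR 1.40.

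In this construction the per-cycle comparison points against surgery while the per-woman comparison points in its favour. Drawing every early conceiver from the better half is the extreme case; a weaker link with prognosis gives a smaller shift.

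**The case against.** The sentence on cancelled cycles sits in the treatment section, just before the three-cycle allowance, and may concern only that allowance. The ART data list records cancellation before pick-up as an item of a cycle, and exact denominators often belong in an analysis plan. This part of the objection stands: the wording is ambiguous. It does not remove the problem, because the adjacent definition ties a cycle to its pick-up on either reading. An analysis plan that took over this definition would inherit the denominator.

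It also stands that every rate above is assumed. Holding live birth per pick-up equal while cancellation triples is a deliberate construction to show the mechanism, not a forecast.

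A reader might infer more than the document supports:

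- **That the trial's main result is compromised.** It is not. The primary endpoint is per participant, under intention to treat, and counts any live birth. A woman whose stimulations are all cancelled and who has no birth is a failure; a spontaneous live birth is a success. The cumulative pregnancy and spontaneous pregnancy rates are also per woman, and the protocol treats secondary endpoints as exploratory.
- **That the protocol expressly excludes women who conceive before ART.** No sentence says so; it follows from the cycle definition.
- **That a fall in ovarian response after surgery would vanish.** It would be attenuated. Oocytes retrieved remains an outcome among women who reach pick-up, so fewer oocytes there would still show. Only cancelled stimulations drop out.

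**Conclusion.** The concern holds for the exploratory per-cycle outcomes only. As defined, they compare subsets formed after randomisation, which sits badly with a statement that all analyses follow intention to treat and with an objective worded as an effect of surgery.

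The direction and size of the bias cannot be read from the protocol. With 30% live birth per pick-up in both arms and cancellation of 5% v 10% to 15%, a per-pick-up RR of 1.00 corresponds to 0.95 to 0.89 per started cycle. Loss of early conceivers from the surgery arm acts separately: if they have better prognosis, it makes surgery look worse per cycle. The two mechanisms may offset or reinforce each other. The point is worth correcting because it is cheap to correct, not because it threatens the primary conclusion.

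**What to change.** Change the definitions and analysis text as follows; the number of cycles offered is not touched.

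1. State separately what counts towards the three-cycle allowance and what counts as a cycle in the analysis.
2. Define the analysis cycle as each started stimulation, from the start of FSH, which the protocol already uses as the start of ART. Score cancellation before pick-up as no pregnancy, no live birth and zero oocytes from that cycle.
3. Make the first started cycle the main per-cycle contrast.
4. Report by arm the share of starts cancelled before pick-up, with reasons, and the share of women who never start ART, showing separately those who conceived first.
5. Add a version over all randomised women, for example live birth from conception before ART or from the first started cycle. Step 2 alone does not recover women who conceive before ART.
6. Keep per-pick-up rates, labelled as conditional and descriptive.

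The cost is mainly wording. Per-cycle rates become slightly lower. Zero oocytes for a cancellation unrelated to response is a blunt score, which is why reasons and per-pick-up figures should stand beside it. Cancellation and its reason are already listed for collection, but the ART data are limited to three cycles and the visit schedule is tied to retrievals. The sponsor must confirm that the case report form captures starts that do not count towards the allowance; if it does not, it needs a small addition.
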